### Circuit Exercise Group

The circuit exercise for the participants in this group will be designed for each participant. To ensure exercise endurance, patients allocated to this group will complete a 6MWT, as prescribed by the American Thoracic Society [25], which will be conducted along a straight 40-m Department of Physiotherapy passageway. On successful completion of the 6MWT, patients will be given an opportunity to familiarize themselves with the circuit exercise equipment. Exercise sessions will take place 3 times a week for 8 weeks. The participants will undergo 10 min of warm up before and 10 min of cool down after the training. The stations for circuit training include 2 stations—1 and 2. Station 1 is the resistance exercise, whereas station 2 is the aerobic exercise with the bicycle ergometer. Station 1 comprises the following 6 substations: station A—bench press, station B—seated row, station C—lateral pull down, station D—biceps forward, station E—front thigh and back thigh, and station F—leg press. Resistance exercises will be performed on weight machines. Throughout the resistance training program, participants will rotate among the different machines until they have used every one: the bench press, seated row, lateral pull down, biceps forward, front thigh, back thigh, leg press, and rowing.

Participants will be instructed to exhale while lifting a weight and inhale while lowering it, to minimize blood pressure excursions, and to rest for 2-3 min between sets. Participants will perform 1 set of resistance exercise 3 times weekly for the first 2 weeks, 4 sets of each resistance exercise 3 times weekly during weeks 3 and 4, and complete set of resistance exercise in the last 4 weeks. For each station, the participants will spend 10 min; this includes the substations. Resistance will be increased by 5-10 kg, once the participant is able to perform more than 15 repetitions while maintaining proper form.

All the aerobic activities of the circuit training will be performed on a cycle ergometer. Participants will be free to vary the machine used from one visit to the next. Exercise intensity will be standardized by using heart rate monitors (Polar Electro Oy) that will display the participant’s heart rate and emit a warning signal if the heart rate goes outside the prescribed training zone, thus guiding the participant to adjust the workload up or down to achieve the desired intensity. In addition, the rate of perceived exertion will be measured using the Borg scale.

### The Routine Care Group (Control Group)

Participants in the control group will receive routine medication as prescribed by the attending physicians at the diabetes clinic and will be monitored. Their prescriptions will be guided by the IDF guidelines. After 8 weeks of routine care, the participants will be enrolled into either the rebound exercise or circuit exercise group. The control group will be given health magazines to read, whereas the exercise groups will be engaged in the exercise programs.

All the 3 groups will receive routine medication and counseling regarding diet, weight control, and information to identify, minimize, or avoid complications of diabetes.

### Measurement

The following measurement would be taken during the data collection they are as follows:

Sociodemographic variables: The sociodemographic variables of the participants will be recorded before the commencement of the study. These include age, race, gender, height, weight, educational level, duration of diabetes, level of pain, blood pressure, pulse rate, and heart rate.Pain intensity: The alternate visual analog scale will be used to assess the pain level of the participants. The participants will be requested to rate on a 0-10 scale, the level of pain they felt 6 weeks before and at present. On the scale, 0 indicates no pain or no interference, whereas 10 is pain as bad as it could be/extreme interference [26]. The alternate visual analogue scale has been reported to have a high validity, increased patient compliance, greater sensitivity of measurement, and reduced bias [26].BDI: This will be used to assess and screen participants for depression. The BDI is a 21-item multiple choice self-reported inventory, widely used to assess the presence and degree of depression in adolescents and adults [27]. The BDI is a self-administered questionnaire and it has a high test-retest reliability (Pearson *r*).QoL: The General Health Survey Short Form (SF-36) will be used to measure changes in the participant’s QoL. The instrument has shown good validity and reliability of Cronbach alpha of .85 and reliability coefficient of .75 for all the domains except social functioning [28]. The short form, SF-36, measures perceived health in the areas of physical functioning, role-physical, bodily pain, general health, vitality, social functioning, role-emotional, and mental health, with higher scores (range 0-100) reflecting better-perceived health.Biochemical parameters: Fasting blood glucose in mmol/L, blood total cholesterol (TC) in mmol/L, low-density lipoprotein (LDL) mmol/L, very low-density lipoproteins (VLDL) mmol/L, and high-density lipoprotein (HDL) mmol/L will be determined at baseline and after 8 weeks of the program. A blood sample will be taken by pinprick using Accu-check Sofclix Pro Roche Diabetes care, South Africa. Then, the following parameters will be evaluated: fasting glucose level using Accutrend (Roche Diagnostics, GmbH Germany); HDL-C using PEG þ cholesterol oxidase (Roche Diagnostics GmbH Germany); triglycerides using glycerol phosphate-PAP (Roche Diagnostics GmbH Germany); and TC using cholesterol oxidase-PAP (Roche Diagnostics GmbH Germany) to evaluate TC, LDL, VLDL, and HDL-C.Pulmonary parameters: Pulmonary function parameters will be measured at baseline and after the 8 weeks of the study using Spiro 232 (PK Morgan, India). The following parameters will be measured: Forced expiratory volume in first second (FEV_1_) (It), forced vital capacity (FVC), FEV_1_/FVC ratio, peak expiratory flow rate, and maximal voluntary ventilation (It/min). The spirometer will be connected to a computer that will record all the values.

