### Rebound Exercise Group

Participants randomized to this group will be instructed on the proper techniques of the desired movements (hopping) on the rebounder. All instruction and training will be provided by the research assistants who are physiotherapists practicing in South Africa. They will teach the participants how to rebound during the session. To ensure exercise endurance, patients allocated to this group will complete a 6-min walk test (6MWT), as prescribed by the American Thoracic Society [25], which will be conducted along a straight 40-m Department of Physiotherapy passageway. On successful completion of the 6MWT, patients will be given an opportunity to familiarize themselves with the equipment. Each participant will undergo 3 sessions a week for 8 weeks, with each session lasting between 15 and 25 min.

The exercise will involve bouncing on the center portion of a mini trampoline (2013 Portable Model Half-Fold Cellerciser) with feet slightly apart and knees in full extension. Each foot strike equals one step or bounce with step height. This will be defined as the distance between the foot at a maximum height of the jump and the bed of the center of the trampoline ranging between 10 and 15 cm [23]. Exercise durations were set at 5-min intervals with 3-min rest periods. Each exercise program session will last 15 min with 9 min of rest for the first 4 weeks, progressing to 25 min with 15 min of rest in the subsequent 4 weeks, 3 times per week over 8 weeks.

Bouncing frequency will be determined by signals from a metronome and will be set at between 90 and 120 bounces per minute. Heart rate training zone will be maintained during the exercise at a moderate intensity of 40% to 60% and will be calculated using the Karvonen formula ([heart rate reserve×training percentage]+resting heart rate) [23]. The heart rate will be monitored using the heart rate monitor (Polar Electro Oy) that will display the participant’s heart rate and emit a warning signal if the heart rate goes outside the prescribed training zone, thus serving as a guide and indicator for the participant to adjust the steps and bounce while on the trampoline. In addition, the Borg scale will be used to assess the rate of perceived exertion.

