### Procedures

Assessment of participants will be conducted at 2 stages: at baseline and at the end of 8 weeks of intervention. To ensure a comprehensive assessment, a battery of measures was chosen covering the WHO-ICF model [30]. Certain tools were selected to cover the 3 key domains proposed by the ICF: body structures and function (hematological variables, MSKP, and respiratory parameters), activity, and participation (QoL and depression). At baseline, participants will be assessed for sociodemographic characteristics, which will include personal demographic information and diabetes-specific information. The personal demographic information will include age, sex, height, weight, marital status, educational qualification, and employment. The diabetes-specific information will include type of diabetes and duration since diagnosis. At the baseline, the outcome measures to be used for these assessments are presented in the measurement section. Table 1 shows the instruments.

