**Figure 1 figure1:**
[figure not shown]
CONSORT flow chart.

**Table 1 table1:** Study assessment tools.

Scales or tools	Function or applications
Metronome	To provide signals for participants during exercises
Mini trampoline	For rebound exercise
Treadmill	For aerobic component of circuit training
Biodata form	To record the sociodemographic variables of participants
Alternate visual analog scale	To assess change in pain scores of participants
Beck Depression Inventory	To assess change in depression of participants
General health survey short form (SF-36)	To assess change in quality of life of participants
Accutrend plus	To assess the fasting glucose-level change and cholesterol-level change in participants
Spiro232	The spirometer will be used to measure change in forced expiratory volume, forced vital capacity, peak expiratory flow rate, and maximal voluntary ventilation

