### Data Analysis

Preliminary analysis will be performed to test the normality of the data using the Kolmogorov V-Smirnov test before the analysis. Demographic data will be analyzed using descriptive statistics, whereas data on QoL and depression will be analyzed within the group using the Wilcoxon signed rank test and between the groups using the Kruskal-Wallis test. Post hoc test will be used for any significant F values.

The paired *t* test will be used within the group for pain scores, fasting glucose, and cholesterol level of the participants and between groups using 1-way multivariate analysis of variance. Post hoc test will be used for any significant F values. The level of significance will be set at .05. The SPSS version 23 will be used for the analysis.

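### The six-week pain recall has no stated visit or role and does not fit an 8-week programme; pain should be the week-8 present rating, adjusted for the baseline present rating

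*Protocol article*

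**What the plan says.** The pain item in the protocol article's Measurement section reads: "The participants will be requested to rate on a 0-10 scale, the level of pain they felt 6 weeks before and at present". This gives two 0-10 ratings, one recalled and one current. The item carries no timing of its own, whereas the biochemical and pulmonary items in the same section are explicitly placed at baseline and after 8 weeks.

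Pain also appears among the variables recorded before the study begins: "educational level, duration of diabetes, level of pain, blood pressure, pulse rate, and heart rate". Which rating this refers to is not stated.

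The visit schedule is in Procedures: "Assessment of participants will be conducted at 2 stages: at baseline and at the end of 8 weeks of intervention". The two exercise programmes fill the interval between the visits: "Each participant will undergo 3 sessions a week for 8 weeks" in the rebound group and "Exercise sessions will take place 3 times a week for 8 weeks" in the circuit group.

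Table 1 gives the purpose of the pain scale as "To assess change in pain scores of participants". Data Analysis says the paired t test will be "used within the group for pain scores, fasting glucose, and cholesterol level of the participants", with one-way multivariate analysis of variance between groups. Neither place names the rating, and no baseline covariate is mentioned.

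**The concern.** A recall window should end or begin at a point that the design cares about. Six weeks does neither here. At baseline it reaches back to pain before the trial, which is harmless. At the end of an 8-week programme it reaches back to a time when the exercise groups are already training.

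With two ratings on the form and one generic term in the analysis, someone preparing the data could pair the recalled with the current rating at the same visit, since a before-and-now pair looks like natural input for a paired t test. At week 8 that pair would miss the first 2 weeks of change. The rating would also come from participants who know their group, because Randomization and Blinding describes blinding of the assessors only.

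Separately, the between-group comparison as written leaves the baseline pain rating unused, although it is collected at no extra cost and is likely to predict the week-8 rating.

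**Working it through.** The protocol states no figure for this item, so there is none to reproduce. The check is calendar arithmetic, followed by the standard variance formulas for baseline adjustment.

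**Where the recall falls**

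Inputs: assessments at weeks 0 and 8 (Procedures); recall of 6 weeks (Measurement); 3 sessions a week for 8 weeks, so 3 × 8 = 24 sessions (both exercise group sections). Recall point = assessment week − 6.

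| Visit | Recall point | Share of programme elapsed | Sessions completed by then |
|---|---|---|---|
| Baseline | 0 − 6 = −6 | none | 0 of 24 |
| Week 8, if asked | 8 − 6 = 2 | 2/8 = 25% | 2 × 3 = 6 of 24 |

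If the item means the whole preceding six weeks, the window at the second visit is weeks 2 to 8, entirely on treatment. On either reading it matches neither study time point.

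**What each contrast would measure**

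- Present rating at week 8 against present rating at baseline: weeks 0 to 8, all 24 sessions.
- Present against recalled rating, both given at week 8: weeks 2 to 8. If benefit built up linearly (an assumption), this holds 1 − 2/8 = 75% of the effect. The share is lower if benefit comes early, and up to 100% if it all comes after week 2.

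**What the baseline covariate gains**

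Let r be the within-group correlation of present pain at baseline and week 8, with equal variances at the two visits. The documents do not give r, so 0.3 to 0.7 is an assumed range. Relative to the variance of an unadjusted comparison of week-8 scores (set to 1), and ignoring the degree of freedom spent on the covariate:

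- change scores: 2(1 − r)
- analysis of covariance: 1 − r²

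| r | Week-8 score alone | Change score | Covariate-adjusted |
|---|---|---|---|
| 0.3 | 1 | 1.40 | 0.91 |
| 0.5 | 1 | 1.00 | 0.75 |
| 0.7 | 1 | 0.60 | 0.51 |

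Since 1 − r² = (1 − r)(1 + r) and 1 + r is at most 2, adjustment is never worse than the change score. Since r² is at least 0, it is never worse than the week-8 score. This matters because Data Analysis does not say which of the two enters the MANOVA.

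**The case against.** The strongest reply is that the article never places the recall at week 8. The item has no timing, pain level is listed among pre-study variables, and musculoskeletal symptoms are an entry condition under Participants. A look-back used once, to describe pain history at entry, fits the text. On that reading nothing falls in week 2, and the recall precedes treatment in every group. Furthermore, two assessments, a scale meant to show change and a paired t test most naturally mean present pain at baseline against present pain at week 8, which the recall does not touch. It can also be said that naming the analysed rating is the kind of detail an article leaves to the full protocol or analysis plan. All of this stands. The missing name alone would not be a finding.

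A reader might be tempted to go further in four ways, none of which the documents support.

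- **That the pain outcome is contaminated.** This requires the recalled rating to be asked at week 8 and used. Neither is stated.
- **That power for pain collapses.** Averaging the two week-8 ratings, with linear build-up, would keep (1 + 0.25)/2 = 62.5% of the effect, so that f = 0.35 becomes 0.35 × 0.625 = 0.22 if the SD is unchanged. With 20 per group, power would fall from about 65% to about 30%. But no averaging is planned, and Sample Size and Power Calculation does not tie f = 0.35 to pain. The SD of an average also shrinks by √((1 + r)/2), r here being the correlation of the two ratings: at r = 0.5, f is 0.22/0.87 = 0.25 and power about 38%.
- **That the false-positive rate reaches 1 − 0.95² = 9.75%.** That needs two independent ratings and a choice of the better result. Two ratings by one person are correlated, which lowers the figure (about 9.1% if the two test statistics correlate at 0.5, about 7.8% at 0.8), and no such choice is planned.
- **That pain is the primary outcome.** The abstract's objective lists it first, but the Objective section lists it after glycemic control, cholesterol and respiratory parameters, and no primary outcome is named.

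What the objection does not remove is that the six-week window is stated without visit or purpose beside an 8-week programme, and that the stated between-group method makes no use of the baseline rating.

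**Conclusion.** The point holds in limited form. The article fixes a recall item badly: if asked at the second visit, it refers to week 2, or weeks 2 to 8, which serves no stated comparison. This follows from the stated schedule alone, but it is conditional on the item being asked then. Harm to the pain result is a further conditional risk, arising only if the recalled rating enters the analysis, and it cannot be given a size from the documents.

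The firmer part is an available improvement. Moving from an unadjusted comparison of week-8 scores to one adjusted for baseline present pain reduces variance by r²: 9%, 25% and 49% at r = 0.3, 0.5 and 0.7. Against change scores the gain at the same values is 1 − 0.91/1.40 = 35%, 1 − 0.75/1.00 = 25% and 1 − 0.51/0.60 = 15%. These figures rest on the assumed r, equal variances at the two visits and a linear relation. The change is worth making, but the plan is not invalid without it.

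**What to change.** 1. In Measurement, define the pain outcome as the present 0-10 rating at week 8, with the same rating at baseline.
2. State that the six-week recall is asked at baseline only and is descriptive, and remove it from the week-8 form.
3. In Data Analysis, say that pain scores means the present rating, and replace the unadjusted one-way comparison of pain between groups with an analysis of covariance (or a multivariate analysis of covariance, if the joint test is kept) that has the baseline present rating as covariate.

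The cost is a few lines of text and one item off a form. No new data are needed, and the adjusted model uses one degree of freedom. What is given up is a week-8 recall that no stated analysis needs. The change does not alter the fact that participants rate their own pain knowing their group.

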
### Sample Size and Power Calculation

The sample size (N) will be determined using Cohen table [29] at alpha=.05 and degree of freedom (µ)=k−1, where k is the number of groups, with effect size f=0.35. From the previous study [17] and power (w) 80%, sample size n=20. Sample size (N) will be 60, and 12 extra participants will be added to make room for attrition. Therefore, the sample size will be 72 participants, and each group will be 24 participants.

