### Theoretical Framework

Previous studies have assessed the effect of combined resistance and aerobic exercises on type 2 DM patients and observed significant reductions in HbA_1c_ [21-23]. However, Geirsdottir et al [24] did not observe any favorable changes in fasting glucose or HbA_1c_ in patients with type 2 diabetes. Therefore, there is no consensus on the effect of CRT in type 2 diabetes. Rebound exercise has been documented to be effective in reducing plasma fasting glucose, HbA_1c_, and body mass index (BMI) in type 2 diabetes. It is also simple, inexpensive and enjoyable [23]. Moreover, it has been documented to improve QoL in patients with type 2 diabetes [17]. However, its effect on MSKP, respiratory parameters, and depression has not been documented. Prospective RCTs on the effects of exercise in the prevention or treatment of musculoskeletal complications, cardiorespiratory parameters, and psychosocial variables seen in diabetes patients are needed [16]. In African countries, there is a paucity of reports that describe musculoskeletal disorders in diabetic patients. To the best of our knowledge, no clinical trial has been conducted that compares the effect of rebound exercises and circuit training on MSKP, respiratory parameters, and psychosocial variables among patients with type 2 diabetes. No previous studies had been conducted to assess the effect of any treatment or prevalence of MSKP manifestations in diabetic patients or to evaluate the predisposing factors. This study is, therefore, proposed to determine the effect of rebound exercises and circuit training on MSKP, as well as selected biochemical and psychosocial factors among individuals with type 2 diabetes.

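### The stated 80% power is for a one-way ANOVA on one unnamed outcome, which is not among the planned between-group tests; on its own inputs that ANOVA has about 65% power at 20 per arm

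*Protocol article*

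**What the plan says.** The Sample Size and Power Calculation section begins "The sample size (N) will be determined using Cohen table [29] at alpha=.05" and sets the degrees of freedom at k−1, "where k is the number of groups, with effect size f=0.35. From the previous study [17] and power (w) 80%, sample size n=20". The total follows from this: "Sample size (N) will be 60, and 12 extra participants will be added to make room for attrition", giving 72 participants, 24 per group. No outcome is named.

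The Data Analysis section assigns the between-group tests by outcome. Quality of life and depression are compared with Kruskal-Wallis. Pain scores, fasting glucose and cholesterol have paired t tests within groups "and between groups using 1-way multivariate analysis of variance". Post hoc tests follow only a significant F, and "The level of significance will be set at .05". The Abstract names only MANOVA for the between-group comparison.

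**The concern.** A power figure is meaningful only for the test it was computed for. Cohen's f with k−1=2 numerator degrees of freedom describes a univariate one-way ANOVA. With three groups and p outcomes, a MANOVA has 2p numerator degrees of freedom: 6 for three outcomes, 12 for six. Its power depends on how many outcomes respond, in which directions, and how the outcomes correlate. A single f does not fix any of these. Kruskal-Wallis is a rank test and is not the sized test either.

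The stake is how a null result would be read. A reader who trusts the 80% would take a non-significant MANOVA as fairly strong evidence against an effect of the assumed size, and the plan does not support that. For pain, glucose and cholesterol, a non-significant MANOVA also means no post hoc comparisons. The fourth objective, comparing the two exercises and routine care, depends on those for these outcomes.

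**Working it through.** **Inputs from the protocol:** k=3 groups, alpha 0.05, f=0.35, n=20 per group (N=60), or 24 per group (N=72) if nobody is lost.

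**Step 1. The plan's own figure.** For a one-way ANOVA, df1=k−1=2, df2=N−3, noncentrality λ=N·f², and power=P(F(df1, df2; λ) > critical F).

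| n per arm | N | df2 | critical F | λ = N × 0.1225 | Power |
|---|---|---|---|---|---|
| 20 | 60 | 57 | 3.159 | 7.35 | 65.4% |
| 24 | 72 | 69 | 3.130 | 8.82 | 74.2% |
| 27 | 81 | 78 | 3.114 | 9.92 | 79.6% |
| 28 | 84 | 81 | 3.109 | 10.29 | 81.2% |

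The stated 80% at n=20 is not reproduced. It would need f of about 0.41 at n=20, or about 0.37 at n=24. Relaxing alpha to 0.10 gives 76.6% at n=20. A two-group comparison with d=2f=0.70 needs 33 per group two-sided or 26 one-sided. The attrition step is arithmetically consistent: 60+12=72, and 72/3=24.

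**Step 2. Sized test against planned tests.**

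| Outcome | Planned between-group test | Same as the sized test? |
|---|---|---|
| Pain, fasting glucose, cholesterol | One-way MANOVA, numerator df 2p | No |
| Quality of life, depression | Kruskal-Wallis | No |

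**Step 3. Can MANOVA power be obtained from the inputs?** The protocol gives no correlations and no multivariate effect size. It also leaves open whether cholesterol enters as one variable (three outcomes) or as total, LDL, VLDL and HDL (six with pain and glucose). The figures below are therefore assumed scenarios. They come from simulation (5,000 runs per cell) with Wilks' lambda and Rao's F, which for three groups is F=((1−√Λ)/√Λ)·((N−p−2)/p) on 2p and 2(N−p−2) df. Group means are equally spaced, all outcomes are equally correlated, and each responding outcome has f=0.35. The rejection rate under the null, with three outcomes, was 4.7%.

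Power at n=20 per arm:

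| Outcomes, pattern | corr. 0 | 0.3 | 0.5 | 0.7 |
|---|---|---|---|---|
| 3, all respond | 94.2% | 75.9% | 64.4% | 54.4% |
| 3, one responds | 43.4% | 50.8% | 65.5% | 86.3% |
| 6, all respond | 99.5% | 73.4% | 55.1% | 42.3% |
| 6, one responds | 31.7% | 40.0% | 54.7% | 81.4% |

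Repeat simulations agreed within a few percentage points, with a lowest value of 31%. At n=24 the same grid runs from 39.4% to 99.9%. The direction of the mismatch is therefore not determined by the protocol.

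**Step 4. Power of a baseline-adjusted univariate test.** For an ANCOVA of the week-8 value on arm and baseline, the effect size becomes f/√(1−ρ²), where ρ is the correlation between baseline and week 8 (an assumption). With N=60, df1=2 and df2=56:

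- ρ=0.3: f=0.367, λ=8.08, power 70%
- ρ=0.5: f=0.404, λ=9.80, power 78%
- ρ=0.7: f=0.490, λ=14.41, power 92%

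**The case against.** The strongest reply is that the mismatch does not show the trial to be underpowered for the MANOVA. This stands. A reader might infer from the larger numerator degrees of freedom that the MANOVA must fall short of 80%, or that it has less than an even chance of success. The documents do not support either reading. The low values arise with one responding outcome and weak correlation. Yet the Results section hopes for improvement in pain, glycemic control and cholesterol together, and several of the assumed cells exceed 80% at n=20. Three outcomes is also the more natural reading of the Data Analysis wording, and the lowest values need six.

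A reader might also infer that f=0.35 was derived for quality of life, because the Theoretical Framework cites reference 17 for that outcome. This cannot be established. The Introduction cites the same reference for managing type 2 diabetes in general, and the sample-size sentence does not make clear whether f comes from it at all.

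Two further points stand. No between-group test is designated primary, and a null MANOVA does not gate the Kruskal-Wallis tests. MANOVA is also a legitimate global test: replacing it for every outcome would be partly a preference, and separate tests each at 0.05 would raise multiplicity.

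None of this rescues the 80%. Both the sized test and the planned tests are stated in the protocol and they differ, so the gap is not a detail left to an analysis plan. The ANOVA shortfall in Step 1 needs no assumption about correlations.

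**Conclusion.** The concern holds in this form: the 80% applies to no planned between-group test, and it is wrong even for the univariate ANOVA it was computed for. There the protocol's inputs give 65% at 20 per arm and 74% at 24, with 28 needed for 80%. These figures rest only on the stated f, alpha and group sizes.

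MANOVA power is undetermined. The range of about 31% to over 99% at n=20 rests on assumed outcome counts of 3 or 6, correlations of 0 to 0.7, and either one or all outcomes responding. It shows that the inputs are insufficient; it does not estimate the trial's power.

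**What to change.** In Sample Size and Power Calculation, name the one outcome to which f=0.35 applies and justify f for it. In Data Analysis, test that outcome between groups with an ANCOVA of the week-8 value on arm and baseline value. If the chosen outcome is quality of life or depression, this replaces its Kruskal-Wallis test.

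Then replace the 80% with the power of that test at 60 completers: 65% unadjusted, or about 70%, 78% or 92% for an assumed baseline correlation of 0.3, 0.5 or 0.7. The assumed correlation should be stated. At 0.5 the power is still slightly under 80%.

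If the MANOVA is kept as the main between-group test, list its outcomes and state the assumed correlations, the multivariate effect and the resulting power instead of 80%. It may remain as a supporting global test in either case.

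The cost is wording in two sections, with no extra patients or measurements, since baseline and week-8 values are already collected. The downside is a stated power that is probably less favourable. Keeping 80% on the unadjusted ANOVA would instead need 84 completers, or about 101 recruited with the same attrition allowance (84 × 1.2 = 100.8).

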**Methods:**

A total of 70 participants are expected to be recruited in this single blind randomized controlled trial. Computer-generated random numbers will be used to randomize the participants into 3 groups, namely, the rebound exercise group, the circuit exercise group, and the control group. Measurements will be taken at baseline and at the end of the 8 weeks of the study. Participants’ musculoskeletal pain will be assessed using the visual analog scale, quality of life will be assessed using the SF 12 Health Survey Questionnaire, depression using the Beck Depression Inventory, respiratory parameters using the spirometer, and biochemical parameters such as glucose level and cholesterol level using the glucometer. Data will be analyzed using descriptive statistics and inferential statistics of multivariate analysis of variance between the groups and paired t test within the group. Alpha will be set at .05.

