### Intervention

The study will comprise 3 groups; the rebound exercise group, the circuit resistance exercise training group, and the routine care group (the control). The routine care group will undergo one exercise training after 8 weeks of enrollment. Participants will be monitored for subjective fatigue, dyspnea, respiratory distress, profuse sweating, or unsteady gait during the exercise activities, as these may be indications that they have reached maximum exertion.

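### The stated inputs do not give 20 per group: at f=0.35 with three groups, 20 per group has about 65% power, not 80%

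*Protocol article*

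**What the plan says.** The calculation is in Methods, Sample Size and Power Calculation:

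- Method and alpha: "The sample size (N) will be determined using Cohen table [29] at alpha=.05".
- Numerator degrees of freedom: "degree of freedom (µ)=k−1, where k is the number of groups". The Intervention section sets out three groups (rebound, circuit, routine care), so k−1 = 2.
- Effect size, power and result: "with effect size f=0.35. From the previous study [17] and power (w) 80%, sample size n=20".
- Total: 60 participants plus 12 for attrition, and then "Therefore, the sample size will be 72 participants, and each group will be 24 participants".

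The Methods paragraph of the abstract gives a different total: "A total of 70 participants are expected to be recruited in this single blind randomized controlled trial".

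The Data Analysis section plans between-group tests by one-way multivariate analysis of variance (pain, fasting glucose, cholesterol) and Kruskal-Wallis (quality of life, depression). It names no baseline covariate. The sample-size section mentions neither a baseline–outcome correlation nor a repeated-measures design.

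**The concern.** The article gives a complete calculation with every input, so it can be checked without the cited earlier study or the cited table. An f of 0.35 lies between the conventional medium (0.25) and large (0.40) values, and 20 per group looks small for it with three groups.

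This calculation is the article's only justification for the size of the trial. If it overstates power, a non-significant result would carry less information than readers are led to think. The objectives include comparing all three conditions, and the Results section expects information on which exercise works best. Comparisons between pairs of arms generally have less power than the overall test, so the shortfall affects those as well.

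**Working it through.** **Inputs.** From the sample-size section: alpha = 0.05, numerator df = k−1, f = 0.35, power 80%, n = 20 per group. From the Intervention section: k = 3.

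**Formula.** One-way analysis of variance, overall F test, with N = 3n:

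- df1 = k−1 = 2 and df2 = N−3
- noncentrality λ = f²·N = 0.1225·N
- power = P(F′(df1, df2, λ) > critical F at alpha 0.05), where F′ is the noncentral F distribution

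**The plan's own figure.** At n = 20, N = 60, df2 = 57 and λ = 0.1225 × 60 = 7.35. The critical F is 3.159 and power is **65.4%**. The stated 80% is not reproduced.

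**Other sample sizes, same inputs.**

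| n per group | N | λ | Power |
|---|---|---|---|
| 20 | 60 | 7.35 | 65.4% |
| 24 | 72 | 8.82 | 74.2% |
| 27 | 81 | 9.92 | 79.6% |
| 28 | 84 | 10.29 | 81.2% |

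The first size to reach 80% is 28 per group (84 evaluable). With the plan's own attrition share of 12/72 = 16.7%, that is 84 / (1 − 1/6) = 100.8, so 101 enrolled, or 102 for equal groups.

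**Effect detectable with 80% power.** f = 0.411 at 20 per group and f = 0.374 at 24 per group.

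**Could another reading give 80% at n = 20?**

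| Variant at 20 per group | Power |
|---|---|
| Large-sample chi-square in place of F | 67.8% |
| alpha = 0.10 | 76.6% |
| Two groups | 57.8% |
| Four groups | 72.7% |
| f = 0.40 | 77.6% |
| 1-df contrast | 76.0% |
| Two-group comparison, d = 0.7 | 60.0% |

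None comes within 2 points of 80%.

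**Baseline adjustment (not in the article).** If the outcome were adjusted for its baseline with correlation r, the effective effect size would be 0.35/√(1−r²). The documents give no r, so it is an assumption and a range is shown, at 20 per group:

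| r | Effective f | Power |
|---|---|---|
| 0.3 | 0.367 | 70% |
| 0.4 | 0.382 | 73% |
| 0.5 | 0.404 | 78% |
| 0.6 | 0.437 | 85% |
| 0.7 | 0.490 | 92% |

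The break-even is r of about 0.53. A repeated-measures calculation gives anything from 73% to above 90%, depending on an unstated correlation and on which effect is tested.

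**Pairwise comparisons (illustrative).** These depend on how the means are arranged, which the article does not say. Two-sample t tests at 20 per group:

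- Both exercise arms equally better than control: d = 0.35/(√2/3) = 0.74 against control. Power is 63% unadjusted, or 45% at alpha 0.05/3.
- Three equally spaced means: adjacent arms differ by d = 0.35 × √6/2 = 0.43, with 26% power. The two extreme arms differ by d = 0.86, with 75% power.

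**Totals.** 3 × 20 = 60, 60 + 12 = 72 and 3 × 24 = 72 agree with each other. The abstract's 70 does not. At N = 70 with no dropout, power is about 73%.

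**The case against.** The strongest defence is that the real analysis may be more efficient than the calculation. Outcomes are measured before and after, and an analysis using the baseline could bring 20 per group to 80% or above. That is true for r of about 0.53 or more. But the article states no correlation, sizes the trial by a between-group method with k−1 degrees of freedom, and plans no baseline covariate. The defence would need a different calculation and a different analysis from those described.

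A second point stands as a limit on what is shown. The planned tests are a multivariate analysis of variance and Kruskal-Wallis, and f=0.35 is tied to no named outcome. The 65% therefore tests the sample-size statement by its own method; it is not the exact power of each planned test.

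Third, the article does not claim 80% power for any pair of arms, and the pairwise figures rest on assumed patterns of means. They show how the shortfall carries over but are not needed for the conclusion.

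Finally, the cited study and table are not available here, so the origin of n=20 cannot be traced. A misprinted effect size is possible, though f=0.40 would still give only 77.6%.

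**Conclusion.** The concern holds. The stated inputs need 28 per group and the article states 20. Power is overstated by about 15 percentage points at the planned 60 completers (65.4% against 80%). It stays about 6 points short at the full 72 with no dropout (74.2%). If f=0.35 is the true effect, the chance of missing it with 60 completers is about 35% (100 − 65.4), not 20%.

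This rests only on the inputs in the article and on the overall one-way F test that its sample-size section implies. It does not depend on any assumed correlation or pattern of means. The difference between 70 and 72 is a separate and minor inconsistency.

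**What to change.** Correct the statement and keep the 72 participants. Suggested wording: *With alpha .05 and three groups, 20 evaluable participants per group give 65% power for f=0.35 by one-way analysis of variance (74% with 24 per group); 80% power is reached at f of about 0.41 with 20 per group and 0.37 with 24.* Change the abstract total to 72. It would also help to add that this power refers to the overall three-group test and not to rebound versus circuit.

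This costs one paragraph and one number in the abstract, with no extra participants. The price is a less favourable stated power.

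There are two alternatives, both dearer:

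- **Size the trial on a baseline-adjusted analysis.** The assumed correlation must then be stated and justified, with power shown over a range (70% at r=0.3 to 92% at r=0.7, at 20 per group). The Data Analysis section would have to change to include the baseline covariate.
- **Keep f=0.35 and 80% power.** This needs 84 evaluable participants, about 102 enrolled at the plan's own attrition share, which is 30 more than planned.
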